**Methods:**

This protocol uses a two cohort unblinded and double-blinded, randomized, pre- and post-intervention methods and crossover matched group design. In Cohort 1, a sample of 106 participants with poor sleep quality will be randomized into two groups. All participants will start with 1 week of no intervention. Group 1 will use theta/delta BBF for 2 weeks followed by 1 week of no intervention followed by music for 2 weeks. Group 2 will do the reverse. In Cohort 2, 62 participants will be blinded and randomized into two groups. Group 3 will use music for 2 weeks followed by a 1-week break followed by music embedded with theta/delta BBF for 2 weeks. Group 4 will do the reverse. Using Cohort 1 music only as a control, data will be collected using sleep actigraphy, sleep quality questionnaires, and sleep diaries with a crossover and match group analysis between cohorts to compare the effect of no intervention vs. music vs. BBF only vs. music with BBF on sleep quality.

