### Power analysis and data analysis plan

For Cohort 1, since the study is comparing three measures, a 2 × 3 mixed ANOVA (between and within subject factor) will be used. The parameters for this analysis were as follows: (1) power of 1—β = 0.85, (2) level of significance of α = 0.05, (3) an autocorrelation parameter (i.e., average correlation) ranging from 0.3 to 0.7 (in increments of 0.2), and (4) a standardized effect size (F) ranging from small (0.1) to medium (0.25) in 0.05 increments. Using GPower software, the sample size estimates range from *n* = 52 (when the correlation of the repeated measures = 0.7 and the standardized effect size is *F* = 0.25) to *n* = 116 (when the correlation of the repeated measures = 0.3 and the standardized effect size is *F* = 0.1). For this study a sample of 106 will be sufficient (84 required, plus 25% for attrition bringing the total to 105 and the addition of 1 to make both arms equal in number).

For Cohort 2, assuming there is no difference in mean sleep efficiency score (i.e., mean difference = 0) between the interventions (BBF only, music with BBF) a sample size of 61 participants (plus 1 to make group equal in number *n* = 62) would be needed to declare with at least 80% power that the intervention effect in BBF only is the same as in music with BBF. Given that Cohort 1 is *n* = 106 and that propensity score matching with replacement will be implemented to make the groups comparable, the final test for intervention effect will be carried out with a power in excess of 80%.

For this two-period 2-arm cross-over design where each subject gets both treatments and repeated outcome measurements over time, a linear mixed model with repeated measures (MMRM) approach will be used. Unless otherwise stated, all statistical tests will be 2-sided with the probability of a Type I error not to exceed 0.05. Descriptive statistics will be used for all quantitative and qualitative variables at all data collection points. Continuous variables will be tabulated using N, mean, standard deviation or standard error (as appropriate), median, minimum, and maximum values. For categorical variables, frequency counts and percentages will be presented.

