Actual values and change from baseline in the different Sleep Actigraphy report outcome variables will be summarized by time point and sequence group using descriptive statistics. Analysis will be conducted for the following variables: number of hours in bed, total number of hours asleep, number of minutes it took to fall asleep, percent efficiency of sleep, number of minutes awaken after sleep onset, and total number of times awaken after falling asleep. Sleep efficiency will be used as the main indicator for improvement of sleep quality and will be calculated by dividing the amount of time spent asleep (in minutes) by the total amount of time in bed (in minutes) and multiplying it by 100. Study parameters include sleep latency <30 min, wakefulness after sleep onset <30 min, decreased frequency in number of awakenings, total sleep time >6 h and sleep efficiency >80%.

Qualitative measures of sleep obtained from the PSQI will be analyzed using descriptive statistics. As for the National Sleep Foundation Sleep Diary entries, summary statistics will be provided at the different data collection time points. To further improve the precision of the estimates, items from the National Sleep Foundation Sleep Diary scores and light exposure (sleeping at night vs. sleeping during the day) may be entered into the model as additional covariates. To assess if the participants' personal characteristics' affect the outcome a two-step modeling approach will be followed. First, the effect of each demographic variable will be evaluated separately in a series of separate MMRM models that include each study outcome as the dependent variable and the demographic characteristic and time as predictors. All demographic factors will then subsequently be entered into a MMRM model that also incorporate intervention, period, sequence as fixed effects, and study participant as a random effect.

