For the match group analysis between Cohorts 1 and 2, propensity score matching will be implemented to construct a sample of subjects which have similar baseline covariate distributions between the cohorts. A logistic regression model, with intervention cohort as the dependent variable, will be employed to estimate the conditional distribution of the intervention given the covariates. The predictors in this model are baseline characteristics believed to be related to the main study outcome of interest (e.g., sleep efficiency score). To make optimal use of the number of subjects enrolled in Cohort 1, a match and replace method will be used whereby a BBF embedded with music user could be matched to more than one BBF only user. This will help maximize the number of matched BBF participants while enhancing the ability of the study to detect a difference in intervention between the two cohorts if indeed there is one.

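### Cohort 2 has no attrition allowance although Cohort 1 has one, and matching with replacement cannot supply it, so the claimed power above 80% for the matched comparison is not assured

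*Protocol article*

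**What the plan says.** All of this is in the protocol article.

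- **Cohort 1** (Power analysis and data analysis plan): 84 are required, 25% is added for attrition to reach 105, and 1 more equalises the arms, giving 106.
- **Cohort 2** (same section): the calculation starts by "assuming there is no difference in mean sleep efficiency score (i.e., mean difference = 0) between the interventions", and gives "a sample size of 61 participants (plus 1 to make group equal in number", that is, 62. The 61 "would be needed to declare with at least 80% power" that "the intervention effect in BBF only is the same as in music with BBF". The abstract confirms the enrolment: "In Cohort 2, 62 participants will be blinded and randomized into two groups". The only addition to 61 is the 1 that makes the groups equal.
- **Power claim** (same section): because Cohort 1 has 106 participants and propensity score matching is with replacement, "the final test for intervention effect will be carried out with a power in excess of 80" per cent.
- **Matching** (same section, paragraph on the match group analysis): one user of music with BBF may be matched to several BBF-only users. The stated benefit is "This will help maximize the number of matched BBF participants while enhancing the ability of the study to detect a difference".
- **Schedule and missing data** (Study procedure and Table 2): both cohorts follow the same weeks 1 to 7, and missing data are not recaptured.

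**The concern.** Two adjacent paragraphs size two cohorts that are randomised from one screened pool and follow one schedule. One paragraph allows for attrition and the other does not, and no reason is given. If 61 is the number needed, 62 enrolled leaves room to lose one person.

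The claim of more than 80% power then rests on two things of different kinds. A larger comparator group does reduce the standard error. Matching with replacement does not add independent people. In the direction the plan describes, the smaller cohort is reused, so distinct Cohort 2 participants stay capped at 62, and unequal reuse lowers their effective number.

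The comparison concerned is the cross-cohort one, BBF only against music with BBF, where the plan hopes to declare the effects the same. A sameness claim needs adequate power. If power is lower than stated, failure to show equivalence becomes likely even when the effects are equal, and readers will have been told otherwise.

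**Working it through.** **1. The plan's own figures.** Cohort 1: 84 × 1.25 = 105, plus 1 = 106. This reproduces. Cohort 2: the 61 cannot be reproduced, because neither an equivalence margin nor an SD of sleep efficiency is stated.

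**2. Loss that the allowance covers.** Keeping 84 of 105 is 80% retained, a 20% loss. Applied to both cohorts:

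- Cohort 2: 62 × 0.80 = 49.6, about 49
- Cohort 1: 106 × 0.80 = 84.8, about 84

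If the 25% is read as the loss itself, 62 × 0.75 = 46.5 (about 46) and 106 × 0.75 = 79.5 (about 79). Applying the plan's method to Cohort 2 would give 61 × 1.25 = 76.25, so 77, or 78 for equal groups.

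**3. Power formula (assumed).** Two one-sided tests (TOST), normal approximation, true difference 0, as the plan assumes:

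power = 2Φ(m/SE − z) − 1, with SE = √(1/n₂ + 1/n₁) in SD units and m = margin/SD.

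The plan gives no TOST level, so both 0.05 (z = 1.645) and 0.025 (z = 1.960) per side were used. Setting power to 80% at 61 fixes m. The comparator behind the 61 is not stated, so three bases were tried:

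| Base for the 61 | m, 0.05 per side | m, 0.025 per side |
|---|---|---|
| 61 v 61 | 0.530 | 0.587 |
| 61 v 84 | 0.492 | 0.545 |
| 61 v 106 | 0.470 | 0.521 |

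Worked example, base 61 v 61 at 0.05, with 49 v 84: SE = √(1/49 + 1/84) = 0.180; m/SE = 2.948; power = 2Φ(2.948 − 1.645) − 1 = 0.807.

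**4. Results** (range over the two levels; every participant weighted equally):

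| Cohort 2 v Cohort 1 | Base 61 v 61 | Base 61 v 84 or 61 v 106 |
|---|---|---|
| 62 v 106, no loss | 90–91% | 80–85% |
| 49 v 84, 20% loss | 81% | 65–73% |
| 49 v 49, 20% loss, 1:1 | 66–67% | 46–57% |
| 46 v 79, 25% loss | 77–78% | 60–69% |
| 46 v 46, 25% loss, 1:1 | 61–63% | 41–53% |

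**5. What replacement does.** As an illustration, 106 Cohort 1 users were each matched to the nearest of 62 Cohort 2 users, with reuse allowed. The assumptions were one random score with the same distribution in both cohorts, no link between score and outcome, and no attrition. About 44 of the 62 were used at all. With effective size taken as (sum of weights)² / (sum of squared weights), Cohort 2 counted for about 30. From the 61 v 61 base, 30 v 106 gives about 63–65%, before any loss.

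**The case against.** Several points on the other side stand.

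- **The larger Cohort 1 is a real gain.** Without loss, 62 v 106 at equal weight gives about 90% if the 61 assumed a comparator of the same size.
- **The plan's own loss rate is 20%, not 25%.** On that rate and the most favourable base, 49 v 84 still gives about 81%. A reader might infer that the stated power has been shown to fail under the plan's own attrition assumption. The documents do not support that, because this reading clears 80%.
- **Completer counts are conservative.** The plan keeps whatever data are collected and uses a mixed model. Group 4 receives music with BBF, and Group 1 receives BBF alone, in the first period. Someone in either group who leaves after week 4 has already supplied data for this contrast.
- **The matching simulation is only illustrative.** The plan chooses predictors believed to relate to the outcome, and matching on those could recover some precision.
- **The 61 might be a total over both interventions.** Power would then stay above 80%, but the text uses 61 to size Cohort 2 alone.

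None of this supplies the missing allowance or gives replacement a role in raising power. The favourable results need little loss together with equal weighting and a particular meaning of 61, and the section states none of these.

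**Conclusion.** The point holds as a claim that is not assured. Cohort 2 has no attrition allowance where Cohort 1 has one, and half of the reason given for exceeding 80% power, matching with replacement, cannot do that work.

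With the loss covered by the × 1.25, power is about 81% at best. It is 66–67% at 49 v 49 from the 61 v 61 base, and 65–73% at 49 v 84 if the 61 was already sized against 84 or 106. A 25% loss gives 77–78% or 61–63% from the 61 v 61 base. Most readings with attrition therefore fall below 80%.

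Every power figure depends on an assumed TOST, on a margin-to-SD ratio back-solved from 80% at 61, and on completers as the analysed set. They show how far the claim depends on unstated choices; they do not estimate the trial's actual power. No stated Cohort 2 arithmetic is wrong. The defect is an omitted term and an unsupported sentence.

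**What to change.** In Power analysis and data analysis plan:

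1. Delete the statement that the final test has more than 80% power, and the appeal to matching with replacement as a reason for it.
2. Restate the power of the matched comparison of BBF only with music plus BBF at the expected completers, about 49 in Cohort 2 and 84 in Cohort 1, using the attrition allowance already adopted for Cohort 1.
3. Give the equivalence margin and the SD behind the 61, and base the restated power on the effective sample size after matching weights.

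This is a change of wording and a recalculation. Enrolment need not change. The cost is a stated power that is likely to be less favourable.

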#### National Sleep Foundation sleep diary (version 6)

The National Sleep Foundation Sleep Diary is a short 15-item questionnaire that captures the daily habits that may influence sleep. The questionnaire is divided into two parts, seven questions to be completed upon awakening and eight questions to be completed at bedtime. Given that most of the questions upon awakening will be captured by the actigraphy monitor, these questions will not be utilized for the study. As for the questions to be completed at bedtime, these address: (1) exercise, (2) medication use, (3) napping, (4) sleepiness during the day, (5) mood, (6) alcohol, food and caffeine intake, (7) timing of caffeine intake, and (8) bedtime routine. This instrument is not scored but will be used to assess patterns and if those patterns affected the sleep outcomes (38). According to the literature, it is recommended that persons wearing actigraphy monitors also use a sleep diary as it captures subjective data that an actigraphy monitor cannot detect (39).

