#### Weeks 1 and 2—Baseline

For the first 2 weeks participants will be instructed to wear the actigraphy monitor and complete the daily sleep diaries to obtain baseline data.

#### Weeks 3 and 4—Intervention 1

Participants will be instructed to use their designated MP3 player at bedtime. Once the play button is pressed, the audio file will automatically play a continuous loop throughout the duration of their sleep. Participants will continue to wear the actigraphy monitor and complete the sleep diaries as in Weeks 1 and 2. If participants find that the audio file prohibits them from sleeping, they are to discontinue its use and to contact the investigator within 24 h. The MP3 players will come with an accompanying USB cable to allow for the participants to charge the device if needed. The actigraphy monitors, which can hold a charge up to 30 days, will be charged by the investigator. In the unlikely event that the monitor fails, whatever data is collected will still be used. However, since it is unclear if there is a dose effect for BBF or music for that matter, participants will not be asked to recapture any missing data as it could impact the outcome measures. If a participant forgets to wear the monitor, they will still be required to complete the sleep diary questionnaire and note it in the questionnaire.

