#### Week 5—Break

For the next week, participants will be instructed to abstain from using any audio stimulation at bedtime but to continue to wear the sleep actigraphy monitor and to complete the daily sleep diaries.

#### Weeks 6 and 7—Intervention 2

The investigator will contact the participant to instruct them to commence using their second intervention. Just as in Weeks 3 and 4, participants will use their respective audio intervention while wearing the actigraphy monitor and completing the sleep diaries. If the music or sound technology prohibits the participant from sleeping, the participant is to discontinue its use and contact the investigator within 24 h.

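### Diary items recorded during the intervention weeks are allowed as covariates in the efficacy model, which can bias the estimated effect of the audio on sleep efficiency

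*Protocol article*

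**What the plan says.** Protocol article, *Power analysis and data analysis plan*: the crossover is analysed with a mixed model for repeated measures, and sleep efficiency from actigraphy is the main indicator. The terms named for the full model are "intervention, period, sequence as fixed effects, and study participant as a random effect", with demographic factors added. Under the aim "To further improve the precision of the estimates", the plan says that "items from the National Sleep Foundation Sleep Diary scores and light exposure (sleeping at night vs. sleeping during the day) may be entered" as further covariates in the model. No diary item is excluded, and nothing says which weeks' values are meant.

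*National Sleep Foundation sleep diary (version 6)*: only the bedtime half is used. Its items include "3) napping, (4) sleepiness during the day, (5) mood, (6) alcohol, food and caffeine intake, (7) timing of caffeine intake".

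*Weeks 3 and 4—Intervention 1*: "Participants will continue to wear the actigraphy monitor and complete the sleep diaries as in Weeks 1 and 2". *Weeks 6 and 7—Intervention 2*: "participants will use their respective audio intervention while wearing the actigraphy monitor and completing the sleep diaries". Table 2 also marks the diary for the break week.

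*Outcomes measures*: separately from the efficacy model, diary items are to be examined for relationships with the sleep outcomes.

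**The concern.** A covariate measured before treatment can sharpen a treatment comparison without changing what it estimates. A covariate measured on treatment can itself be changed by the treatment. If the audio improves sleep, participants may be less sleepy, nap less, feel better and drink less caffeine the next day, and those changes may affect the following night. Holding them fixed removes that route from the estimate, so the intervention coefficient is no longer the total effect of the audio on sleep efficiency. If the item and the outcome also share an unmeasured cause that varies over time, such as a stressful week, adjustment can create an association that the randomised order had excluded. At stake is the meaning of the main contrast between BBF and music, and in the shared-cause case its Type I error.

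**Working it through.** **1. Which values the wording covers.** The propensity model for matching the cohorts is expressly built on baseline characteristics. The sentence on diary covariates has no such limit. Its aim is precision, and values from before the intervention can add almost none. A covariate X that is constant across periods enters the within-participant difference as β(X − X) = 0, so it leaves the period contrast unchanged. The stated aim therefore fits values that vary by period or night.

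**2. Timing.** Each intervention period is two weeks with a daily diary, so about 14 bedtime entries. If the audio starts on the first night, only the first entry precedes all audio in that period; the other 13 follow at least one such night.

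**3. Whether the items can respond.** The protocol's own text says so. *Sleep quality* lists alertness and mood among the things that poor sleep harms. *The efficacy of using binaural beats frequencies for sleep quality* suggests that BBF during sleep may have made listeners more alert the next day. *Study design* reports lower daily stress with BBF in Phase 1.

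**4. Size of the bias (illustration).** The documents give no effect size and no response of any diary item, so there is no stated figure to reproduce. Write

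- item: M = person + aT + noise (within-participant SD 1)
- sleep efficiency: Y = person + period + cT + bM + error

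where T is 1 on BBF and 0 on music. The total effect is c + ab. Adjusting for M returns c, so the bias is −ab.

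Inputs: n = 84 (the required number before attrition for Cohort 1) and two-sided α = 0.05, both from the protocol. Assumed: total effect 3.0 points, participant SD 6, residual SD 5, b = −2 points per SD of the item. Each scenario was simulated 2,000 times, regressing the period difference on treatment with and without the item.

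| Shift a in item (SD) | ab | Adjusted estimate, 3.0 − ab | Simulated estimate | Power, adjusted | Power, unadjusted |
|---|---|---|---|---|---|
| 0 | 0 | 3.0 | 3.02 | 96% | 94% |
| −0.25 | 0.5 | 2.5 | 2.50 | 87% | 94% |
| −0.5 | 1.0 | 2.0 | 1.98 | 65% | 94% |
| −0.75 | 1.5 | 1.5 | 1.52 | 40% | 95% |
| −1.0 | 2.0 | 1.0 | 1.01 | 18% | 96% |

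As a check on the simulation, the unadjusted SE should be √[2(5² + 2²)/84] = √(58/84) = 0.83; the runs gave 0.83.

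**5. Other directions.** If the item acts the opposite way (b = +2, a = −0.5), then ab = −1 and the adjusted estimate is 3.0 + 1.0 = 4.0 (simulated 4.01).

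Now let the audio have no effect on sleep efficiency (b = c = 0) but shift the item by −0.5 units. Let an unmeasured cause raise the item by 1 unit and sleep efficiency by 3 points per SD. The item's slope in the adjusted model is then 3/(1 + 1) = 1.5, and the false effect is 0.5 × 1.5 = 0.75 points. The simulation gave 0.74, with rejection in 14.7% of runs against 5.6% unadjusted.

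**The case against.** **The wording permits; it does not commit.** It names no item and no week, and the terms fixed for the model are the standard crossover ones. The choice of items and weeks is commonly left to a statistical analysis plan, which is not shown. This stands in part: the absence of a selection rule is not a defect, and a reader who infers that the choice will be made after seeing results goes beyond the documents. What remains is that the text allows, for the outcome model, an adjustment that can change what is estimated.

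**Bedtime entries come before that night's audio.** They therefore cannot carry the same night's effect. This is correct for a night-level model, but they do carry effects of earlier nights in the period. The problem is larger if period averages are entered; the protocol does not say which form is meant.

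**The direction is not fixed.** This stands. A reader might infer that adjustment necessarily removes part of the effect, but step 5 shows inflation and a false effect, and the first row of the table shows no bias. Less daytime sleepiness, for example, could also mean less sleep pressure the next night.

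**The items differ.** Exercise, alcohol, food and bedtime routine are less clearly affected by the audio. Night or day sleeping, which the protocol links to shift work, is much less exposed to the objection and can be a legitimate covariate.

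**Conclusion.** The point holds as a conditional one. The protocol permits adjustment for diary values recorded on treatment, several of those items can respond to the audio, and using them would mean that the intervention coefficient is not the total effect on sleep efficiency. Partial loss of the effect is the most plausible result; inflation or a false effect is possible; an item that does not respond to the audio causes no such bias.

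The size is unknown. The fall from 3.0 to about 2.0 points, and every power figure above, rests on the assumed total effect, SDs, item slope and item response.

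Two stronger readings are not supported. A particular loss of power cannot be claimed for this trial, because the documents supply none of those inputs. Nor do they show that the protection of randomised order is lost in the main analysis: the harm is confined to a model that uses this optional adjustment with responsive items. The wording should still be corrected before analysis.

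**What to change.** State that the primary efficacy model contains intervention, period, sequence and participant, and that any diary covariates added to it are limited to values from before the first intervention (Weeks 1–2). Do not enter diary items from Weeks 3–7, in particular daytime sleepiness, mood, napping and caffeine. The break week is included because it follows the first intervention. Keep these items for the exploratory relationship analyses in *Outcomes measures*. Night or day sleeping may remain a covariate where it is set by the work schedule.

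This is a wording change and needs no new data. The cost is whatever precision night-level or period-level diary behaviour would have added. In the illustration with an item that does not respond to the audio, that is an SE of 0.825 instead of 0.771, and power of 94.0% instead of 96.3%. Because Weeks 1–2 values nearly cancel from the within-participant contrast, they will not recover that precision, so in practice the fix comes close to leaving diary items out of the efficacy model.

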#### Cohort 1 (n 106) unblinded

Group 1: Baseline → theta/delta BBF alone → 1 week break → music aloneGroup 2: Baseline → music alone → 1 week break → theta/delta BBF alone

Since the participants in Cohort 1 will know when they are receiving the intervention, it could be argued that their outcomes are due to a placebo effect, therefore a second cohort using a different group of participants will be used.

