### Study procedure

#### Screening, consenting, and randomization process

Once the participants have been screened using the inclusion and exclusion criteria, they will sign an Institutional Review Board approved consent and randomized into two cohorts using block randomization. This process was chosen as it reduces bias and increases the probability that the group in each cohort will contain an equal number of individuals (4). Participants in Cohort 1 will then be randomized into Groups 1 or 2 while participants in Cohort 2 will be randomized into Groups 3 or 4.

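### The cohorts are said to be randomised, so propensity matching between them removes no bias and costs precision; the contrast is also open-label versus blinded, which neither matching nor adjustment can remove

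*Protocol article*

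**What the plan says.** All references are to the Protocol article.

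- **How cohorts are formed** (Screening, consenting, and randomization process): participants are "randomized into two cohorts using block randomization", and then randomised again to a sequence group within their cohort.
- **How cohorts are compared** (Power analysis and data analysis plan): "propensity score matching will be implemented to construct a sample of subjects which have similar baseline covariate distributions between the cohorts". Cohort membership is the dependent variable of a logistic model. The sample-size paragraph gives the reason: "propensity score matching with replacement will be implemented to make the groups comparable". The direction is one-to-many: "a match and replace method will be used whereby a BBF embedded with music user could be matched to more than one BBF only user". No ratio, caliper or variance method is given.
- **Claimed benefit** (same section): matching is said to make the best use of Cohort 1 and to help detect a difference, and the final test is said to have more than 80% power.
- **Blinding** (the two cohort descriptions): Cohort 1 is unblinded. Cohort 2 is added because, for Cohort 1, "it could be argued that their outcomes are due to a placebo effect". Cohort 2 is blinded, and each of its participants has a music-alone period.
- **Control** (abstract, Methods): "Using Cohort 1 music only as a control".

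**The concern.** Propensity matching is a remedy for groups that were not formed by chance. On the text as written, these were. The randomisation section and the analysis section therefore rest on different pictures of the same trial, and only one can be right.

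If the randomisation text is right, matching solves no problem. It weights some Cohort 1 participants several times and may leave others out, which costs precision in the comparison for which Cohort 2 was sized. That matters here because the stated goal is to declare the two BBF conditions the same, and such a claim needs a narrow interval.

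What does differ systematically between the cohorts is blinding. Balancing baseline covariates, by matching or by regression, leaves that difference untouched.

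**Working it through.** **1. The plan's own figure.** Cohort 2's 61 participants cannot be reproduced, because no equivalence margin or SD is given. Assume two one-sided tests at 0.05 each, true difference 0 (as the plan assumes) and 61 per group. In SD units:

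- SE = √(2/61) = 0.181
- margin = SE × (z₀.₉₅ + z₀.₉₀) = 0.181 × (1.645 + 1.282) = 0.53 SD

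This 0.53 SD is an assumption implied by 61 per group. It is not in the document. If 61 is read as a total, the implied margin is 0.75 SD.

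**2. Precision of matching when cohorts are random.** Inputs from the plan: 106 and 62 participants, matching with replacement. Assumptions: six baseline covariates, one correlated 0.6 with outcome; nearest neighbour on the logit; no caliper; each Cohort 2 participant matched to k in Cohort 1. Variance is relative to baseline-adjusted regression on all 168.

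| Analysis | Relative variance | Cohort 1 participants used (of 106) |
|---|---|---|
| Adjusted regression, everyone | 1.0 | 106 |
| Unadjusted, everyone | about 1.6 (theory: 1/(1 − 0.6²) = 1.56) | 106 |
| Matched 1:1 | about 2.2 | about 42 |
| Matched 1:2 | about 1.7 | about 66 |
| Matched 1:3 | about 1.5 | about 81 |
| Matched 1:4 | about 1.4 | about 90 |
| Matched 1:5 | about 1.3 | about 95 |

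A repeat run agreed to within about 0.1. A separate set-up with five covariates jointly explaining 0% to 30% of the variance gave 1.9 to 2.1 at 1:1 and about 1.5 at 1:2.

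**3. The power claim.** Power = 2Φ(0.53/SE − 1.645) − 1, with empirical SEs from the five-covariate set-up (R² = variance explained by the covariates):

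| Analysis | R² = 0 | R² = 0.3 | R² = 0.5 |
|---|---|---|---|
| Matched 1:1 | SE 0.224, 53% | SE 0.190, 75% | SE 0.184, 79% |
| Matched 1:2 | SE 0.195, 72% | SE 0.165, 88% | SE 0.150, 94% |

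Using everyone without adjustment: SE = √(1/106 + 1/62) = 0.160, power 90.5%. With adjustment at R² = 0.3: SE 0.133, power 98%.

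Under this assumed margin, matched power lies between 53% and 94%. Power above 80% is possible but not assured, and matching is not what would deliver it.

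**4. Could each cohort's own music period rescue the cross-cohort contrast?** Take the difference of differences, (music plus BBF − music) in Cohort 2 minus (BBF − music) in Cohort 1. With equal variances and a common correlation ρ:

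- baseline-adjusted direct contrast: variance ∝ 1 − ρ²
- difference of differences: variance ∝ 2(1 − ρ)
- ratio = 2(1 − ρ)/(1 − ρ²) = 2/(1 + ρ)

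At the plan's ρ of 0.3, 0.5 and 0.7 the ratio is 1.54, 1.33 and 1.18. It is less precise throughout that range. It also still carries expectation, because the BBF − music difference in Cohort 1 is open-label.

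**5. Which control?** Music plus BBF is given only in blinded Cohort 2, where every participant also has blinded music alone. Setting it against Cohort 1's music swaps a blinded within-person control for an unblinded one from other people.

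**The case against.** **The cohorts may not really be randomised.** The abstract describes randomisation only within each cohort, Cohort 2 is introduced as a different group of people, and each cohort has its own sample-size argument. If they are enrolled separately, matching is a recognised method. This stands as a reason to reconcile the text. It does not rescue matching as the better choice, since covariate adjustment on the full sample would serve there too.

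**The loss depends on an unstated ratio.** This stands. The plan describes one-to-many matching, so 1:1 is the worst case, and from 1:3 upward matching is more precise than an unadjusted comparison of everyone. A reader might infer that most of Cohort 1 is discarded; at 1:5 about 95 of 106 are used. In none of the ratios examined does matching equal adjusted regression.

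**The standard error may be handled properly.** A reader might infer that reuse of participants is ignored and the Type I error inflated. The document does not state the variance method, so this is conditional only. If reuse were ignored, simulated rejection at a nominal 5% was about 6.5% to 7.6%.

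**The blinded evidence survives.** A reader might infer that the plan undoes the purpose of Cohort 2. It does not. The within-person contrast of music with music plus BBF in Cohort 2 remains, and the crossover mixed model covers it. Confounding of BBF alone with blinding comes from giving BBF alone only in Cohort 1, and matching did not create it. The Cohort 1 music control appears in one clause of the abstract; the matching text concerns BBF only versus music plus BBF.

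**Conclusion.** The concern holds in a limited form, and the plan should be changed. On the stated design, matching is unnecessary and inefficient: about 1.3 to 2.2 times the variance of adjusted regression on everyone, from 1:5 down to 1:1. It does not in itself bias the estimate. These sizes rest on random cohort membership, 106 versus 62 participants, one covariate correlated 0.6 with outcome and no caliper. The statements about optimal use of Cohort 1 and power above 80% are not supported by anything shown.

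The cross-cohort contrast is confounded with open-label versus blinded use under any analysis. The abstract's choice of control also disregards the blinded music period that Cohort 2 already provides.

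**What to change.** 1. In the Power analysis and data analysis plan, replace matching with one baseline-adjusted mixed model on all participants of both cohorts. Include sequence, period, mean baseline sleep efficiency and a random participant effect. Fit the four cohort-by-audio cells, so that the direct contrast and the difference of differences are separate, named contrasts. Remove the claims that matching makes optimal use of Cohort 1 and secures power above 80%.
2. Name Cohort 2's own music period as the control for music plus BBF, and correct the abstract to match.
3. State that every cross-cohort contrast, direct or difference of differences, is confounded with open-label versus blinded use. Report any difference of differences as supportive only, given its lower precision.
4. Reconcile the randomisation section with the analysis section. If the cohorts are enrolled separately, correct the randomisation text and still adjust for covariates on the full sample.

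The cost is wording: no extra participants, visits or data. The remaining limitation is that BBF alone versus music plus BBF cannot be separated from blinding in this design.
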